A pelvic examination will be conducted in which samples for RTI testing and cervico-vaginal HIV viral load will be collected, and colposcopy will be conducted. A rapid semen detection test will be conducted on the CVL to determine if the CVL is contaminated with semen which could effect the HIV viral measurement in the CVL, resulting in an inaccurate measurement of the study participant’s cervico-vaginal HIV viral load. If the CVL is contaminated with semen, this CVL and corresponding swab will be discarded, and the enrollment visit will be rescheduled within 48 hours.

Patients in whom the rapid semen detection test is positive will receive extensive counseling regarding risk of HIV transmission to sex partners and strongly encouraged to use condoms or remain abstinent during the study. Regardless of reported partner status, all study participants will be counseled to use condoms consistently throughout the study.

After the baseline examination and clinical specimen collection, women will be randomized to a study arm sequence. If the first arm of her study sequence is a product arm, she will be given instructions on how to insert the product and, while in the examination room, will vaginally insert the first applicator of gel. She will wait either in the examination room or in the waiting room. After approximately 15 minutes, another pelvic examination will be conducted, cervico-vaginal HIV viral load samples including 2 vaginal swabs and 2 CVL (unless further study indicates that only one is necessary) will be collected, and colposcopy will be done. Neither the woman nor the research team will know which of the two products she is using.

If the first study arm to which the participant is randomized is the arm of the study in which noproduct is used, she will also wait at the clinic for 15 minutes and will have a repeat pelvic examination with cervico-vaginal HIV sample collection and colposcopy.

Women assigned to a product arm will be instructed to insert the gel vaginally once daily for the following 6 days. Women will be given 7 applicators (one extra) to take home.

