Follow-up visit #2 (day 14):

The second follow-up visit (day 14) (for those assigned to a product arm, this visit occurs7 days after the woman has stopped using the product), includes the following (See Tables 1-3):

- Pelvic examination
- Vaginal pool pH, and Gram stain specimen collection
- HPV testing
- Sample for cervico-vaginal HIV viral load
- Clinician study form

Women will then be asked to return to the clinic to begin the next study arm 3-5 days after the next menstrual period has ended.

Baseline visit:

The baseline visit will be the first visit of the new study arm. Women using depo provera will be placed on a regular 28 day schedule, so that day 0 will be approximately day 28 of the preceding cycle. In the event that a participant begins the study and she is unable to start her second or third study arms on time, we will allow the woman to start her next arm the following month. The Baseline visit, similar to the enrollment study visit, will include the following (See Tables 2 and 3):

- Interviewer-administered enrollment interview
- Collection of blood sample for plasma HIV viral load testing, HSV 1 and 2 antibody testing
- Baseline pelvic and colposcopic examinations
- Baseline sample collection for RTIs
- Baseline sample collection for cervico-vaginal HIV viral load
- Product administration (if a product arm)
- Second pelvic and colposcopic examinations (to assess acute effects of the product on the vaginal epithelium)
- Second sample collection for cervico-vaginal HIV viral load (to assess acute effects of the product on cervico-vaginal HIV viral load)
- Clinician study form

(The second examination and sample collection will not be conducted at the final study visit, day 28 of the third study arm).

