## Specimen collection and laboratory studies

The following samples will be collected for HIV and RTI testing when indicated in the protocol (see Table 2):

1. Blood (venipucture) for HIV and CD4 count will be conducted once at the beginning of the study.
2. HIV plasma viral load will be conducted at each baseline, a total of three times
3. Cervical/endocervical swab will be used to collect a pap smear specimen once at the second screening visit
4. Cervical swab for HPV testing at screening visit #2 and at each of the day 14 visits, a total of 4 swabs
5. Swabs (2) of the posterior fornix and endocervix for diagnosis of sexually transmitted infections will be collected at the second screening visit and day 28 of the 3rd arm, and repeated if signs or symptoms of STI develop during the study period (Total swabs’ 4).
6. Swabs (2) of the posterior fornix for Gram stain and pH, will be collected at each study visit in which an exam is conducted (Total swabs’22 )
7. Syphilis serologic testing will be conducted once at the beginning of the study unless a genital ulcer or other suggestive symptoms are identified
8. CVL specimens will be collected during each study visit in which a clinical exam is conducted, to measure cervico-vaginal HIV viral load by introducing 5 ml of PBS into the vagina and collecting the pooled fluid in the posterior vaginal fornix. A total of 16 CVLs will be obtained from each woman during the study.
9. Two vaginal swabs will be used during each pelvic exam during the study to collect cervico-vaginal HIV viral load samples (20 swabs). At the second exam (“acute effects” assessment) on day 0 of each arm, four swabs will be used to collect the cervico-vaginal HIV viral load samples (12 swabs)(Total swabs’ 32).

9) Urine pregnancy test at screening #2 and each baseline visit (4 urine samples)

10) Genital ulcer sample collection (if genital ulcer present clinically)

11) A swab will be collected at each study visit to test for semen contamination (11 swabs)

12) HSV-1 and HSV-2 serology on stored blood specimens from all baseline clinic visits (Total of 3 visits per woman - 180 stored specimens total).

13) Cytokine testing on stored CVL specimens from all baseline clinic visits and all day 7 visits (Total of 6 visits per woman - 360 stored specimens total).

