## Data analysis

Objective 1: Product safety

Primary endpoints include epithelial disruption based upon colposcopic and naked-eye exams, vaginal flora disturbances, self-reported symptoms, and acquisition of RTIs. A random effects general linear model will be used which includes parameters for subject effects, treatment effects, period effects and first-order carry-over effects.

##

Objective 2: Genital shedding of HIV

Analyses will be based on a log transformation of the genital tract HIV viral load data, as suggested by preliminary data on genital tract HIV shedding from the CDC laboratory studies (unpublished). A random effects linear model will be used to analyze the data collected at the first follow-up visit, 7 days after daily product use. This model includes parameters for subject effects, treatment effects, period effects and first-order carry-over effects (defined as carry-over effects from the previous period). The subject effect will be treated as a random effect with a normal distribution. The random error term associated with a specific period and subject within a given sequence will be assumed to have a normal distribution with a compound symmetric (uniform) covariance structure. The chosen model assumes no sequence effect, which is reasonable given subjects are being randomized to each sequence. In addition, we assume no treatment by period interaction (i.e. the effect of genital tract HIV shedding for each treatment does not depend on the period it is administered), which seems to be a reasonable assumption for this study. Wash-out periods of three weeks between each treatment are expected to lessen the chances of observing a significant carryover effect. However, since little is known about the effects of these treatments on genital tract HIV viral load, the possibility of a carry-over effect will be tested. In the absence of carry-over effects, this will be dropped from the model and we can estimate the direct effect of the treatments on genital tract HIV viral load.

Objective 3: Product acceptability

Results from the Acceptability questionnaires will be tabulated, and associations between baseline demographic and sexual behavior characteristics and indicators of acceptability will be explored.

Weekly reports on enrollment and follow-up statistics will be distributed by Chiang Rai Health Club staff to the study team to assess trends.

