**Appendix 5: Table 2. Schedule of clinic visits and data collection**

| Study visit | Screen #1 | CRH referral visit | Screen #2 | Male  partner  visit | Enrollment | Follow-up #1 | Follow-up #2 | Baseline | Closing |
| --- | --- | --- | --- | --- | --- | --- | --- | --- | --- |
| Study day | ~ (-30) | ~ (-21) | ~ (-14) |  | Day 0 | Day 7 | Day 14 | Day 0/28 | Day 28,  3rd arm |
| Menstrual day (~28 day) |  |  | Mid-cycle |  | 3-5 days after menses | 10-12 | 17-19 | 3-5 days after menses |  |
| *Specimen collection* |  |  |  |  |  |  |  |  |  |
| HIV test | X |  |  | X |  |  |  |  |  |
| CD4 count | X |  |  |  |  |  |  |  |  |
| RPR | X |  |  |  |  |  |  |  |  |
| Urine preg test |  |  | X |  | X |  |  | X |  |
| HIV viral load |  |  |  |  | X |  |  |  |  |
|  |  |  |  |  |  |  |  |  |  |
| Pap smear |  |  | X |  |  |  |  |  |  |
| Gram stain, ph |  |  | X |  | X | X | X | X | X |
| Gonorrhea, chlamydia |  |  | X |  |  |  |  |  | X |
| Trich In-pouch test |  |  | X |  |  |  |  |  | X |
| Pelvic exam |  |  | X |  | X | X | X | X | X |
| HPV |  |  | X |  |  |  | X |  |  |
|  |  |  |  |  |  |  |  |  |  |
| Colpo |  |  |  |  | X (baseline)  X (15 min) | X |  | X (baseline)  X (15 min) | x |
| CV swab for HIV |  |  |  |  | X (baseline)  X (15 min.) | X | X | X (baseline)  X (15 min.) | X |
|  |  |  |  |  |  |  |  |  |  |
| CVL |  |  |  |  | X (baseline)  X (15 min.) | X | X | X (baseline)  X (15 min.) | X |
| Product application |  |  |  |  | X |  |  | X |  |

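### Acquisition of RTIs is a primary safety endpoint modelled by arm, but routine gonorrhoea, chlamydia and trichomonas tests fall only at screening and closing, so their results cannot be assigned to an arm

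*Protocol*

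**What the plan says.** **Endpoint and model.** Protocol, Data analysis, Objective 1: "Primary endpoints include epithelial disruption based upon colposcopic and naked-eye exams, vaginal flora disturbances, self-reported symptoms, and acquisition of RTIs". The next sentence gives the model: "A random effects general linear model will be used which includes parameters for subject effects, treatment effects, period effects and first-order carry-over effects". The Adverse events section counts all RTIs except HPV as adverse events, asymptomatic ones included, so silent infections are in scope.

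**Schedule for the three STIs.** Specimen collection and laboratory studies, item 5, says that the posterior fornix and endocervical swabs "will be collected at the second screening visit and day 28 of the 3rd arm, and repeated if signs or symptoms of STI develop", and totals them at 4 per woman. In Appendix 5, Table 2, the row "Gonorrhea, chlamydia" and the trichomonas InPouch row are each marked under Screen #2 and Closing only.

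**Schedule for BV and yeast.** Management of RTIs and item 6 of the specimen list place Gram stain and pH at every visit with an examination, for a total of 22 swabs. Table 2 agrees.

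**Text that does not fit the STI schedule.** The Follow-up visits section lists "Baseline sample collection for RTIs" at the baseline visit that opens each new arm. The Enrollment visit section says: "A pelvic examination will be conducted in which samples for RTI testing and cervico-vaginal HIV viral load will be collected". Neither names the infections.

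**The concern.** A model with treatment, period and first-order carry-over terms uses one outcome per woman per period. For gonorrhoea, chlamydia and trichomonas the routine schedule gives one post-enrollment result, taken after Carraguard, placebo and no product have all been completed. An asymptomatic infection from any of the three arms, or from the roughly two weeks between second screening and enrollment, looks the same at closing.

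Increased risk of RTIs is a product risk that the protocol itself names. If these closing results were entered into an arm comparison, a finding of no difference would come largely from the schedule. An analysis plan could not repair this, because the specimens that would date the infections would not exist.

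The text also leaves sites unsure what to collect. On one reading of the baseline and enrollment visits the three STIs are sampled around each arm; on the other they are not.

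**Working it through.** **1. Do the protocol's swab totals match the two-visit schedule?**

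- STI swabs: 2 per visit × 2 visits (second screening, closing) = 4. Stated: 4. Reproduced.
- Gram stain and pH swabs: 2 per visit × (1 second screening + 3 visits × 3 arms + 1 closing) = 2 × 11 = 22. Stated: 22. Reproduced.
- If the RTI samples at the baselines of arms 2 and 3 were STI swabs: 2 × 4 = 8. With enrollment as well: 2 × 5 = 10. Neither equals the stated 4.

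The specimen list and Table 2 therefore agree with each other. The visit descriptions differ from both, unless they mean Gram stain and pH only.

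**2. What is tested when**

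| Visit | Gonorrhoea, chlamydia, trichomonas (item 5, Table 2) | BV, yeast (item 6, Table 2) | Visit descriptions |
| --- | --- | --- | --- |
| Second screening | routine | routine | RTI samples |
| Enrollment (day 0, arm 1) | none routine | routine | RTI samples; pH and Gram stain also listed |
| Day 7, each arm | if signs or symptoms | routine | pH, Gram stain |
| Day 14, each arm | if signs or symptoms | routine | pH, Gram stain |
| Baseline, arms 2 and 3 | if signs or symptoms | routine | RTI samples; Gram stain not listed separately |
| Closing (day 28, arm 3) | routine | routine | not itemised separately |

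**3. Can an arm effect be estimated?** Take 60 women, 10 in each of the six sequences.

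- *One closing result per woman.* The linear predictor is μ + n_A·τ_A + n_B·τ_B, where n_A and n_B count the arms that the woman has completed. Every woman has n_A = n_B = 1, so all three columns of the 60 × 3 matrix are the same and its rank is 1. Neither Carraguard minus placebo nor Carraguard minus no product is estimable. This form lets arm effects add up regardless of order, that is, with no clearance and no treatment between arms.
- *One result per woman per period.* Columns: 1 intercept + 2 period + 2 treatment + 2 carry-over = 7. Rows: 60 × 3 = 180. The rank is 7, and both contrasts are estimable. This is the position for BV and yeast. It would also be the position for the three STIs if they were sampled at the baselines of arms 2 and 3.

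**4. How many infections could be involved?** Follow-up is about 60 women × 3 arms × 28 days = 60 × 84 = 5,040 woman-days; 5,040 / 365.25 = 13.8 woman-years. The protocol gives no STI incidence. Assuming 5 to 20 per 100 woman-years:

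- whole trial: 13.8 × 0.05 = 0.7 to 13.8 × 0.20 = 2.8 infections;
- per arm: one third of that, about 0.2 to 0.9.

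**The case against.** The case on the other side has four parts.

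- **RTIs are more than these three infections.** A reader might infer that no arm effect on RTI acquisition can be estimated at all. The protocol does not support that. It manages BV and candidiasis as RTIs and Gram-stains for both at every examination visit. This stands and limits the point to gonorrhoea, chlamydia and trichomonas. BV may, however, also be counted under the separate endpoint of vaginal flora disturbances.
- **Some infections will be dated within an arm.** Testing is triggered by clinical signs as well as symptoms, and women have pelvic examinations at days 0, 7 and 14 of every arm. This stands for infections that show themselves. Those without symptoms or signs are still first seen at closing.
- **The baseline visit text may already provide the tests.** If its RTI samples include the three STIs, arms 2 and 3 each have a test at both ends, and arm 1 has one at second screening and one at its end. This is possible. It is equally possible that the line means the Gram stain, which that visit's list does not otherwise mention although Table 2 requires it. The text does not settle it, and the swab total of 4 counts against the wider reading.
- **Little would be lost.** Women are abstinent or have one HIV-infected partner, are screened and treated before entry, and receive condoms and counselling. With the few infections expected, even full per-arm testing would give an imprecise comparison. This stands and lowers the severity. It does not make a closing result attributable to an arm.

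**Conclusion.** The point holds for the routine tests of gonorrhoea, chlamydia and trichomonas. Under item 5 of the specimen list and Table 2, they yield one result per woman after all arms, and the Objective 1 model cannot estimate an arm effect from them. Only tests prompted by symptoms or signs within an arm can be dated. Arm effects on BV and candida remain estimable. Separately, the enrollment and baseline visit descriptions conflict with the specimen list and Table 2 unless their RTI samples mean Gram stain and pH only.

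A reader might go further and infer that any true product effect would show as a rate ratio of exactly 1.0, or that two thirds of silent infections would be credited to the wrong arm. Both figures need closing infections to be assigned to the last arm, and the protocol contains no such rule. They also need infections to persist without clearance or treatment until closing; with clearance, closing prevalence would depend weakly on arm order. They should not be quoted as properties of this plan.

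Severity is moderate. The expected 0.7 to 2.8 infections rest on an assumed incidence, and precision would be low under any schedule. What changes is whether the trial may claim an arm comparison for these infections.

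**What to change.** Reconcile the Enrollment visit section, the baseline visit list under Follow-up visits, item 5 of the specimen list and Appendix 5, Table 2. State in Data analysis, Objective 1, which RTIs make up the endpoint and whether BV counts there or under vaginal flora disturbances. Then take one of two routes.

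1. **If the visit descriptions mean Gram stain and pH only:** say so there. Limit the modelled arm comparison to BV and candida. Report gonorrhoea, chlamydia and trichomonas descriptively, with no arm attribution for infections first found at closing. Cost: text only.
2. **If they mean STI swabs:** correct item 5, its total and Table 2 to show these tests at the baselines of arms 2 and 3, and compare each result with the preceding arm, with the closing test serving arm 3. Cost: 2 × 60 = 120 further test sets, at examinations already scheduled. If enrollment is included, so that arm 1 also starts from a test on day 0, it is 3 × 60 = 180.

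Under either route, state that few such infections are expected and that a lack of difference between arms is weak evidence of safety for these three.

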# Objectives

The objectives of the proposed study are to assess the effect of daily vaginal use of Carraguard gel by HIV-infected women on

- Safety
- Genital tract HIV shedding
- Product acceptability

Endpoints will be measured at the first follow-up visit (on study day 7), at the second follow-up visit (on study day 14, 7 days after discontinuing product use), and the next baseline visit (on study day 28, 21 days after discontinuing product use) and will be compared with the baseline assessment on day 0.

Acute effects of the product will be measured 15 minutes after the first application (enrollment visit).

Objective #1: To assess safety

Safety of daily product use will be determined by:

1. Symptoms of irritation
2. Effect on vaginal flora
3. Vaginal epithelial disruption as determined by naked eye inspection (and colposcopic inspection on day 7), according to established guidelines (16), and
4. Other adverse effects (which may include UTI or other unforeseen problems)

Objective #2: To assess effect on genital tract HIV viral load

Genital tract HIV will be measured using samples collected by CVL and vaginal swab, and viral load determinations will be performed using the COBAS AMPLICOR HIV-1 MONITOR v.1.5 Test Kit. In addition, levels of infectious virus will be determined using the multinuclear activation of a galactosidase indicator (MAGI) assay that identifies infectious cell-free HIV-1 in vaginal secretions.

Objective #3: To assess product acceptability

Women will be asked to complete an interview-administered questionnaire regarding acceptability of the product once each study arm at the first follow-up visit (day 7), after using the product daily for 7 days.

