## Sample size

The two primary hypotheses in this study are that Carraguard is 1) different from placebo and 2) different from no product. A primary outcome is cervico-vaginal HIV shedding measured after 7 days of daily product use. The power calculation is based on ensuring adequate power for testing these two hypotheses with this outcome with an overall significance level of 0.05. We used a 3x3 Williams design to determine power/sample size (see graph below). The Williams design is a cross-over design balanced for first carry-over effects when testing products used in sequence and will provide minimum variance unbiased estimates for the treatment effect comparisons in the presence of first order carry-over effects. It is not known whether the washout period used in this study design will be sufficient to assume no carry-over effects, hence a Williams design was employed to ensure unbiased minimum variance estimates. If there are no carry-over effects (i.e. the power will be higher than indicated) the power calculations for this design are conservative.

The null hypotheses for these primary hypotheses are: 1) No difference between Carraguard and no product and 2) no difference between Carraguard and placebo.

In order to carry out the power calculations the within subject variability needs to be specified, as well as an effect size, defined here as the average difference between a pair of treatments. Estimates of the underlying variability of genital tract HIV shedding are based on preliminary data from the CDC laboratory studies (unpublished), where the vaginal viral load was measured weekly throughout the menstrual cycle (i.e. for three weeks after menses) for 45 HIV-infected women. Based on a one-way repeated measures ANOVA, the within standard deviation of cervico-vaginal HIV shedding on the log scale was estimated as 0.66.

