The following plot shows the power to detect a statistically significant difference between a pair of treatments for varying effect sizes with an overall sample size of 30 or 50, at a significance level of 0.025 (based on the Bonferroni adjustment for the two planned pairwise comparisons, for an overall Type I error rate of 0.05). A horizontal line indicates 80% power. The effect size is based on the difference between a pair of treatment means on the log scale. Thus the plot shows that with a sample size of 30 and a within standard deviation of 0.6, there is at least 80% power to detect a difference between a pair of treatment means (on the log scale) of 0.55 or higher. On the other hand, with a sample size of 50 and a standard deviation of 0.6, there is at least 80% power to detect a difference between a pair of treatment means (on the log scale) of 0.43 or higher. The estimates of power would be higher if no carryover effect truly exists. Sixty women will be enrolled to account for participants lost to follow-up and participants who may start antiretroviral therapy and so there is an equal number of women in each study sequence.

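### The primary shedding model leaves out the pre-product day-0 viral load collected in every arm; adjusting for it could sharpen the comparison, by an amount that depends on a correlation the protocol does not give.

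*Protocol*

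**What the plan says.** The Objectives section says that endpoints at day 7, day 14 and the next baseline visit "will be compared with the baseline assessment on day 0". The Data analysis section, under Objective 2, is more specific about shedding: "A random effects linear model will be used to analyze the data collected at the first follow-up visit, 7 days after daily product use". It then lists the terms: "This model includes parameters for subject effects, treatment effects, period effects and first-order carry-over effects". No day-0 term and no change from day 0 appears.

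The day-0 measurement exists in every period. The Enrollment visit section, the Baseline visit list under Follow-up visits, and Table 2 (Appendix 5) all schedule a lavage and vaginal swab for viral load before product is applied, and the no-product arm follows the same schedule. The only analysis use named for the later baselines is in the Study plan: delayed effects at day 28 and carry-over from the previous arm.

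On power, the Sample size section states: "The two primary hypotheses in this study are that Carraguard is 1) different from placebo and 2) different from no product". Each is tested "at a significance level of 0.025 (based on the Bonferroni adjustment for the two planned pairwise comparisons".

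**The concern.** The Data analysis section lists the model terms, so the absence of day 0 is a stated choice and not a detail left open. It leaves the promise in the Objectives without a counterpart in the primary shedding analysis.

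A random subject effect removes what is constant about a woman across the three periods. It does not remove what changes from one cycle to the next. The Background ties shedding to plasma viral load, CD4 count and local inflammation, and any of these can shift over the months of participation. Day 0 and day 7 of one period are a week apart, whereas day-7 samples of successive arms are about four weeks apart or more. If a woman's shedding drifts between cycles, her own day-0 value carries information about her day-7 value that the planned model discards. At stake is the precision of the two primary comparisons.

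**Working it through.** **Inputs.** From the Sample size section: alpha 0.025 per comparison, taken as two-sided; N = 30 or 50; SD 0.6 in the worked power figures; estimated within-woman SD 0.66, from weekly samples over one cycle in 45 women. From Data analysis: subject, period, treatment and first-order carry-over effects. Not in the documents: r. The range 0 to 0.5 is assumed.

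**Step 1: the plan's own figures.** The protocol says "We used a 3x3 Williams design to determine power/sample size". With six sequences, three periods and carry-over in the model, the variance of a pairwise difference is 1.25 × 2 × SD²/N. Error degrees of freedom are 3N − 1 − (N − 1) − 2 − 2 − 2 = 2N − 6. Power is from the noncentral t distribution.

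- N = 30, SD 0.6: power at 0.55 is 80.5% and the 80%-power difference is 0.547. This matches "there is at least 80% power to detect a difference between a pair of treatment means (on the log scale) of 0.55 or higher".
- For the second figure, "with a sample size of 50 and a standard deviation of 0.6", power at 0.43 is 82.1% and the 80%-power difference is 0.419, consistent with the claim of at least 80% power. N = 48, a multiple of six, gives 0.428 and 80.4%, closer to the printed 0.43.

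**Step 2: the planned model at the estimated SD.** N = 50, SD 0.66: variance = 2.5 × 0.4356/50 = 0.02178, SE 0.148, 94 degrees of freedom. Power at 0.43 is 74%; the detectable difference is 0.46.

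**Step 3: effect of using day 0.** Covariate adjustment multiplies the residual variance by 1 − r². A change score multiplies it by 2(1 − r).

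| r | Covariate: variance factor | Power at 0.43 | Detectable difference | Change score: variance factor | Power at 0.43 |
|---|---|---|---|---|---|
| 0 | 1.00 | 74% | 0.46 | 2.0 | 42% |
| 0.2 | 0.96 | 76% | 0.45 | 1.6 | 51% |
| 0.3 | 0.91 | 78% | 0.44 | 1.4 | 58% |
| 0.5 | 0.75 | 86% | 0.40 | 1.0 | 74% |

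A generalised least squares check of a joint day-0/day-7 model with carry-over gave savings of 0–2% at r = 0, 10–11% at 0.3 and 26–27% at 0.5, close to r².

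**Step 4: if r comes from drift.** The SD of 0.66 was measured within one cycle and holds no between-cycle variance. If drift alone produces r, the day-7 residual variance becomes 0.66²/(1 − r). At r = 0.2, power at 0.43 goes from 63% unadjusted to 65% adjusted; at r = 0.5, from 42% to 54%. The relative saving r² is unchanged, but the absolute powers fall.

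**Step 5: carry-over into day 0.** Day-0 values in periods 2 and 3 follow earlier product use. A directly precedes B in two of the six sequences (A-B-C and C-A-B) and never precedes itself. Suppose a carry-over of 0.43 from A reaches the next day 0 but not the next day 7, the true A − B difference is 0.43, and the carry-over term has been dropped. The mean day-0 value is then 0.43/3 = 0.143 higher in B periods than in A periods. With a within-woman slope of about r, the adjusted difference is 0.43 + 0.143r: 0.47 at r = 0.3 and 0.50 at r = 0.5. The unadjusted model returns 0.43. If the same carry-over also reaches day 7 and the term is dropped, the unadjusted estimate is 0.43 − 0.143 = 0.29, and adjustment moves it towards the truth (0.29 + 0.143 × 0.3 = 0.33). With the carry-over term kept, that term absorbs the shift and the adjusted estimate is unbiased.

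**The case against.** The strongest case against is that nothing is shown to be lost. Randomised sequences and a subject effect give a valid comparison without day 0. Drift common to all women is absorbed by the period effects. At r = 0 the gain is nil or nearly so, and at r = 0.1 power moves only from 73.7% to 74.1%. All of this stands. A reader might infer that power is being thrown away for nothing; the documents do not support that, because they give no r and the one-cycle pilot cannot show cycle-to-cycle drift.

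A reader might also infer that the protocol has two competing primary analyses, a day-7 value and a change from day 0. It does not. The Sample size section defines the outcome after seven days of use, its power figures concern treatment means, and Data analysis models day-7 data. The sentence in the Objectives is general, covers all endpoints and names no model. The change-score figures above therefore show which form of adjustment to avoid; they do not describe a planned analysis.

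The objection that adjustment can introduce bias is correct under the conditions in Step 5. It matters because the protocol would drop the carry-over term if carry-over is judged absent, and because it says it is not known whether the washout is sufficient. This sets a condition on the fix but does not defeat it.

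**Conclusion.** The point holds in a conditional form. The stated model omits a pre-product measurement that is collected in every arm and that the Objectives say will be used for comparison. The planned analysis remains valid; the question is efficiency and consistency.

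The variance saving is about r², from none at r = 0 to 25% at r = 0.5, or 74% to 86% power at 0.43. This rests on 50 evaluable women, a day-7 within-woman SD of 0.66, a two-sided 0.025 test with carry-over in the model, and an assumed r. The absolute powers are optimistic if drift adds to that SD.

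**What to change.** In the Objective 2 shedding model only:

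- Add the period's pre-product day-0 log viral load, from the same specimen type as the outcome, split into the woman's mean and her deviation from that mean. Modelling day 0 and day 7 jointly is an acceptable alternative.
- Keep the first-order carry-over term whenever day 0 is adjusted for, whatever the carry-over test shows.
- Report the unadjusted model as a sensitivity analysis.
- In the Objectives, state that for shedding the comparison with day 0 is made by covariate adjustment and not by change score, which is less precise than the planned model when r is below 0.5. Leave the interim mucosal safety comparison from baseline to day 7 as it is.

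**Cost.** No new data and about two degrees of freedom, with no gain if r is near 0. Keeping the carry-over term costs nothing against the protocol's power figures, which already include it. Against a model with the term dropped, it costs the factor 1.25 in variance: at SD 0.66 and N = 50, unadjusted power at 0.43 is 83% without the term and 74% with it. Adjustment makes up that difference when 1.25(1 − r²) falls below 1, that is, when r exceeds about 0.45.
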